## 12.7 Randomized Period, Visit 8: Final Safety Visit (Day 21)

The following activities take place at Visit 8 (Day 21), which is the final safety visit.

| Randomized Period
Visit 8: Final safety visit
(Study Day 21) |        |                                                                                                                                                                                                                                                                                                                                                                                                  |
|--------------------------------------------------------------------|--------|--------------------------------------------------------------------------------------------------------------------------------------------------------------------------------------------------------------------------------------------------------------------------------------------------------------------------------------------------------------------------------------------------|
| Component                                                          |        | Procedure                                                                                                                                                                                                                                                                                                                                                                                        |
| Administrative/
Regulatory                                      |        | 
 
• Explain procedures to be performed at this visit
 
• Confirm/update locator information
 
• Provide reimbursement for study visit
 
• Schedule next study visit, if applicable
 
                                                                                                                                          |
| Clinical                                                           |        | 
 
• Update concomitant medications
 
• Assess vital signs and weight
 
• Perform complete physical exam
 
• Obtain urine sample
 
• Obtain blood samples
 
• Perform pelvic exam with relevant sampling, if indicated (after confirmation of negative pregnancy test) and bimanual exam
 
• Assess AEs
 
 |
| Laboratory                                                         | Urine  | 
 
• <math>\beta</math>-hCG
 
• Dipstick UA
 
• Urine culture, only if indicated
 
                                                                                                                                                                                                                                                    |
|                                                                    | Blood  | 
 
• Hematology, Chemistry, Coagulation (see Section 10.8)
 
• ADA
 
                                                                                                                                                                                                                                                                         |
|                                                                    | Pelvic | 
 
• Vaginal pH, if indicated
 
• Wet mount, if indicated
 
                                                                                                                                                                                                                                                                                  |

## 12.8 Randomized Period, Visit 9: Closing Visit (Study Day 28)

Day 28 is a short outpatient visit, primarily to obtain a final blood specimen for ADA testing. A final urine pregnancy test will be done and AEs will be assessed. No other procedures are scheduled on Day 28, unless indicated.

| Randomized Period
Visit 9: Closing Visit
(Study Day 28) |        |                                                                                                                                                                                                                                                                                              |
|---------------------------------------------------------------|--------|----------------------------------------------------------------------------------------------------------------------------------------------------------------------------------------------------------------------------------------------------------------------------------------------|
| Component                                                     |        | Procedure                                                                                                                                                                                                                                                                                    |
| Administrative/
Regulatory                                 |        | 
 
• Explain procedures to be performed at this visit
 
• Confirm/update locator information
 
• Provide reimbursement for study visit
 
• Schedule next study visit, if applicable
 
                                      |
| Clinical                                                      |        | 
 
• Update concomitant medications
 
• Obtain urine sample
 
• Obtain blood sample for ADA testing
 
• Perform physical exam, only if indicated
 
• Perform pelvic exam, only if indicated
 
• Assess AEs
 
 |
| Laboratory                                                    | Urine  | 
 
• <math>\beta</math>-hCG
 
• Dipstick UA, only if indicated
 
• Urine culture, only if indicated
 
                                                                                                                             |
|                                                               | Blood  | 
 
• ADA
 
                                                                                                                                                                                                                                      |
|                                                               | Pelvic | 
 
• Vaginal pH, if indicated
 
• Wet mount, if indicated
 
                                                                                                                                                                              |

## 12.9 Unscheduled Visits

Subjects will be encouraged to call or visit the clinic between regularly scheduled follow-up visits if they experience any problems. Unscheduled visits (those between regularly scheduled follow-up visits) may occur at the subject's request or as deemed necessary by the investigator or designee at any time during the study. Unscheduled visits may occur for administrative reasons, such as, if the subject has questions for study staff or requires additional study supplies. Interim contacts and unscheduled visits may also occur in response to AEs experienced by subjects, in which case study staff will assess the reported AE clinically and provide or refer the subject to appropriate medical care. All interim contacts and unscheduled visits will be documented in subject's study records and on applicable case report forms.

## **13. OTHER STUDY EVALUATIONS/PROCEDURES**

### **13.1 Pharmacokinetic/Pharmacodynamic Sampling**

Please refer to the Specimen Collection manual of the SSP manual for details on PK/PD sampling.

### **13.2 Biohazard Containment**

As the transmission of HIV and other blood-borne pathogens can occur through contact with contaminated needles, blood, and blood products, appropriate blood and secretion precautions will be employed by all personnel in the drawing of blood and shipping and handling of all specimens for this study as recommended by the US Centers for Disease Control and Prevention (CDC) and the NIH (US).

All biological specimens will be transported using packaging mandated by the US Code of Federal Regulations (CFR) 42 Part 72.

All dangerous goods and materials, including diagnostic specimens and infectious substances, must be transported according to instructions detailed in the International Air Transport Association (IATA) Dangerous Goods Regulations. Biohazardous waste (including used applicators returned to the study site) will be contained according to institutional, transportation/carrier, and all other applicable regulations.

### **13.3 Dye Stain Assay**

An analytic method utilizing a blue dye stain has been established whereby applicators inserted into the vagina can be distinguished from those that have not. The DSA was developed by the Population Council as an objective marker to assess adherence to gel use in clinical trials. The DSA is designed to help investigators determine if microbicide gels are being used and to complement safety and efficacy analyses. The DSA has been validated for use with multiple applicators containing various microbicide products (Wallace et al. 2004; Wallace et al. 2007; Katzen et al. 2011).

The polypropylene applicators being used for this study were specially designed to undergo DSA testing, and were utilized in the context of a Phase 1 trial of another microbicide candidate delivered using the same applicator (Friedland et al. 2016). Please refer to the SSP manual for further details on collection and storage of applicators, which will be tested using the DSA at the Center for Biomedical Research (CBR) of the Population Council.

### **13.4 Follow-up Procedures for Subjects who Discontinue Study Product**

Subjects who choose to discontinue study product will be terminated from the study. A final safety assessment will be conducted for all women who are terminated early, as outlined in the SSP manual.

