#### 14.2.3 Reporting Period for Adverse Events

The reporting period for AEs is the period immediately following the signing of the ICF through seven days after the final dose in the OL period and through 14 days after the final dose in the randomized period of the study.

For the purpose of data analysis, if a non-serious AE has not resolved at the end of the study-reporting period, it will be documented as still ongoing in the CRFs. However, the Investigator must make every effort to follow the event to stabilization or resolution and report the findings/outcome to the Sponsor as soon as possible. A minimum of 3 attempts to follow up with the subject with different methods of communication (e.g., telephone, certified mail, email) should be documented.

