### 15.3.2 Related Grade 2 AEs; Grade 3 and 4 AEs

Individual subjects who develop a related Grade 2 AE, or Grade 3 AE, regardless of relatedness to study drug, will be evaluated by the PI, Medical Monitor and Medical Safety Director for possible discontinuation from the study. Individual subjects who develop a Grade 4 AE, regardless of relatedness to study drug, will be evaluated by the PI, Medical Monitor and Medical Safety Director and discontinued from the study.

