## 15.5 Criteria for Early Termination of Study Participation

Subjects may voluntarily withdraw from the study for any reason at any time. In addition, the Investigator may withdraw subjects from the study for any of the following reasons:

- Indeterminate or positive HIV-1 rapid test
- Acquisition of an STI
- Other medical reasons, including symptomatic vaginal infection diagnosed after enrollment
- Pregnancy
- Report of use of post-exposure prophylaxis (PEP) for HIV exposure
- Report of use of prohibited medications as described in Section 9.8.2
- Subject is unable or unwilling to comply with required study procedures or has failed to follow protocol requirements, including failure to use study product, in a manner judged by the site investigator to be severe enough to affect study outcomes

- Subject might be put at undue risk to their safety and wellbeing by continuing product use, according to the judgment of the Investigator.
- The study Sponsor, government or regulatory authorities, including FDA and Office for Human Research Protections (OHRP), or site IRB terminates the study prior to its planned end date.

Every reasonable effort should be made to complete a final evaluation of subjects who withdraw or are withdrawn from the study prior to completing follow-up. Study staff members will record the reason(s) for all withdrawals in subject's study records.

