### **15.6 Subject Withdrawal**

Subjects withdrawing from the study will not be replaced. Safety data will be included in the analysis from any subjects who withdraw. All efforts should be made to contact any subject who decides to withdraw from the trial. All final safety evaluations should be performed. The main reason for discontinuation prior to completing follow up will be recorded. If a subject discontinues due to an AE, the reasons must be submitted on the IRE forms for SAEs and AE leading to discontinuation. The Council's Study Manager will be informed with respect to enrollment and withdrawals from the study.

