## 17.8 Statistical Analysis of Exploratory Endpoints

Concentrations of GRFT and CG in CVLs will be measured for each subject before and after the first dose. All subjects in the OL period will have CVLs collected 24h post-dose. In the main study, one-half of subjects will be randomized to CVL specimen collection at 4h after the first dose (n=10) and the other half will be randomized to CVL specimen collection 8h after the first dose (n=10). Mean concentration, minimum and maximum will be calculated and concentrations will be summarized for subjects sampled at the three different time points.

Log-normal generalized linear mixed models will be used to analyze changes between baseline and post-gel use in anti-HIV activity of CVL in explants and in concentrations of immune mediators in CVL.

Anti-HIV activity in CVL will be also assessed using a TZM-bl assay with the HIV-1ADA-M laboratory strain. Assays will be performed on serial dilutions to establish a dose-response curve. GraphPad Prism software will be used to prepare curve-fitting analysis and to calculate the median cytotoxicity concentration ( $CC_{50}$ ) and the half-maximal effective concentration values ( $EC_{50}$ , based on CVL dilution or drug concentrations) for all CVLs. Correlations between levels of GRFT in CVL and its anti-HIV activity will be calculated.

Transcriptome will be analyzed using Deseq2 and Voom software to evaluate statistical significance of changes in gene expression in tissue between baseline and post gel application.

Vaginal swabs will be collected to determine potential changes in microbiome post-gel exposure relative to pre-exposure. The unique fraction metric (UniFrac) will be used to measure the differences between microbial communities using the phylogenetic information. Linear discriminant analysis Effect Size (LEfSe) will be employed to compare the microbiome communities before and after gel application.

ADA will be assessed qualitatively both in baseline serum samples and in serum samples collected after daily GRFT use (Day 14), one week after the last gel application (Day 21) and two weeks after the last gel application (Day 28). Shift tables will be presented by treatment arm to summarize changes in detection of ADA between baseline and Days 14, 21 and 28.

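### In the randomized period, stopping the gel means leaving the study, so the 14-day adverse event window has no scheduled contact and the post-dosing antibody draws are not assured

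*Protocol*

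**What the plan says.** On stopping product, protocol section 13.4 has two sentences: "Subjects who choose to discontinue study product will be terminated from the study", and "A final safety assessment will be conducted for all women who are terminated early, as outlined in the SSP manual". Section 15.3 is headed as dealing with discontinuation of study product, but 15.3.2 speaks of the study. Related Grade 2 and any Grade 3 events lead to evaluation for possible discontinuation from the study. Women with a Grade 4 event "will be evaluated by the PI, Medical Monitor and Medical Safety Director and discontinued from the study". The opening of section 15, by contrast, treats temporary holds and permanent discontinuation of product as categories of their own.

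On what follows exit, section 15.5 says "Every reasonable effort should be made to complete a final evaluation of subjects who withdraw or are withdrawn". Section 15.6 adds "All final safety evaluations should be performed", keeps withdrawn women's safety data in the analysis, and states "Subjects withdrawing from the study will not be replaced".

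On the time to be covered, section 14.2.3 runs AE reporting "through 14 days after the final dose in the randomized period of the study". Section 14.3.2 does the same for SAEs, and 17.6 summarises treatment-emergent events (TEAEs) over the same 14 days. None of the three makes an exception for early stoppers. Section 10.9.3 fixes ADA serum at pre-dose and Days 14, 21 and 28. Section 17.8 describes the last two as one and two weeks after the last application and plans shift tables from baseline to each day.

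**The concern.** This is the first use of GRFT in humans, and safety is the primary objective. A woman who stops the gel early may have stopped because of how she tolerated it, so her follow-up is worth keeping. The protocol merges two events that it distinguishes elsewhere: ending product and ending participation. Followed as written, the exit rule leaves the 14-day reporting window without a visit to serve it, and ADA sampling is tied to study days that she may never reach. At stake are late or additional AEs and antibody conversion after exposure ends, in an arm small enough for one woman to change the description of the result. The issue is confined to the randomized period: the open-label period has one dose, a 7-day window and no ADA sampling.

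**Working it through.** There is no sample size calculation to reproduce. Section 17.3 gives 20 randomized women, 14 of them active, and says that no formal calculation was made. The check is one of dates and of the weight of one woman.

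**Dates.** For a last dose on Day d, the reporting window in 14.2.3 ends on Day d + 14. The one- and two-week reads fall on Days d + 7 and d + 14. The fixed draws on Days 21 and 28 fall 21 − d and 28 − d days after the last dose.

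| Last dose (Day d) | d + 7 | d + 14 (window ends) | Day 21 is, after last dose | Day 28 is, after last dose |
|---|---|---|---|---|
| 3 | 10 | 17 | 18 days | 25 days |
| 5 | 12 | 19 | 16 days | 23 days |
| 8 | 15 | 22 | 13 days | 20 days |
| 11 | 18 | 25 | 10 days | 17 days |
| 14 | 21 | 28 | 7 days | 14 days |

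The last row reproduces the plan: for a woman who completes dosing, Days 21 and 28 are one and two weeks after the last dose, and Visits 8 and 9, which both include AE assessment and ADA, cover the window. In every other row the fixed days do not match the description in 17.8.

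**What remains after early exit.** Appendix 2 has no early-termination column and no ADA mark under unscheduled visits. The one final safety assessment can be read in two ways:

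- If it takes place at stopping, up to 14 days of the window have no scheduled contact. For a stop before Day 14, none of the three post-baseline ADA draws is provided for.
- If it is a Visit 8-type assessment about 7 days after the last dose, the first week is covered and one ADA draw is obtained, because section 7.5 describes Visit 8 as a final safety assessment with an ADA draw. Days 8 to 14 after the last dose and the two-week ADA read still have no provision.

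**Weight of one woman.** The active arm is at most 14, and 9.4 says that enrolling all 20 will not be feasible. Each active woman is therefore at least 1/14 = 7.1% of the arm.

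Illustration, resting on an assumption: all 14 active women are enrolled, one stops early and converts, and the other 13 stay negative. With her sampled, the result is 1/14 = 7.1% (exact 95% interval 0.2% to 33.9%). Without her it is 0/13, with upper limit 1 − 0.025^(1/13) = 24.7%. The main change is not in the width of the interval but in whether any conversion is reported.

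**TEAE window.** Section 14.2.1 ends the TEAE window 7 days after the last dose and classes later events as non-treatment-emergent. Section 17.6 uses 14 days for the randomized period. An event 10 days after the last dose is thus a TEAE under 17.6 and not one under 14.2.1.

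**The case against.** The strongest reply is that the protocol does not abandon these women. A final safety assessment is required for everyone terminated early, and 15.5 and 15.6 repeat it. The reporting period in 14.2.3 and 14.3.2 formally still runs 14 days. Unresolved AEs must be followed towards stabilization or resolution with at least three documented contact attempts, SAEs until resolution, and women are told to report events to the site. Timing and content of the assessment may be set in the manual. All of this stands. It makes the problem a gap in scheduled contact, not a proven loss of data.

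Four stronger readings are tempting, and the documents do not support them:

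- A reader might infer that early stoppers leave with neither AE follow-up nor any ADA sample. The required final assessment and its possible ADA draw rule out that certainty.
- A reader might infer that the reported AE rates will look too favourable. A woman who stops for a reaction is already a case, under TEAEs and under TEAEs leading to discontinuation. Section 15.6 keeps her data, and 17.4 keeps her in the safety population.
- A reader might infer a distorted comparison of the arms. The plan in 17.2 is descriptive, and no between-arm safety test is specified.
- A reader might size the loss from the 10% dropout in 17.3. That figure does not separate the reasons for leaving, and no rule can retain women who withdraw consent.

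It is also true that 13.4 covers women who choose to stop, and that 15.3.2 requires exit only for Grade 4. That early stoppers are especially informative about safety is a reasonable inference, not something the protocol states.

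**Conclusion.** The point holds as a gap created by a stated rule. In the randomized period the protocol equates stopping product with leaving the study, and it provides no scheduled contact to the end of its own 14-day AE and SAE window. The ADA draws are not assured for a woman who stops early; even on the favourable reading that the single assessment resembles Visit 8, the two-week post-dosing read is not provided for. What may be missed is later or additional AEs and ADA conversion, with each active woman at least 7.1% of her arm.

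The weight is moderate. Capture of TEAEs bears on the primary endpoint, but the event that caused a stop is already counted, and ADA is exploratory. The conclusion rests on the protocol text alone: the manual could time the assessment differently, but a manual does not change the exit rule or supply the second contact in the protocol. How many women will stop early is not known from the documents.

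**What to change.** In 13.4, 15.3.2 and 15.6, separate product discontinued from study exit. Unless consent is withdrawn, keep a randomized woman who stops the gel in follow-up, with AE assessment and the existing ADA draw 7 and 14 days after her own last dose, in place of Visits 8 and 9. Add this to Appendix 2. In 17.8, report post-dosing ADA by time since last dose; for women who complete all 14 doses nothing changes, since Days 21 and 28 are those times. Section 15.7 already follows a woman terminated for pregnancy beyond her last visit, so the principle is not new to the protocol.

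In the same amendment, reconcile the 7-day TEAE definition in 14.2.1 with the 14-day window in 17.6.

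The rules on when product is stopped are not touched. The cost is a few sentences in the protocol, matching consent text, and up to two short visits, of a kind already scheduled, for each woman who stops early.
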